| Research Title       | Effectiveness of a Five-Component Multimodal Intervention on Executive Function in Children with Autism Spectrum Disorder: A Randomized Controlled Trial                                                                                                                                                                                                                                                                                                                                                                                                                                                                                                                                                                                                                                                                                                              |
| Eligibility criteria | Qualified health professionals will recruit participants through an impartial screening process that adheres to predefined inclusion and exclusion criteria. Children aged 4–18 years of both sexes with a confirmed ASD diagnosis according to DSM-5 and CARS-2, assessed by a child psychiatrist, and who consent to participate in a 12-week intervention will be included. Participants will be excluded if they have cerebral palsy, Down syndrome, ADHD, or any recent (past six months) muscle injury, sprain, head injury, skin laceration, or other conditions that may hinder exercise or study outcomes. Children in the healthy control group will undergo the same interview to confirm typical development and will complete the same outcome measures to compare whether the ASD group can achieve normal developmental levels after the intervention. |

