## Institutional Review Board (IRB)

Department of Physiotherapy & Rehabilitation

Jashore University of Science & Technology

mail: [[contact]](mailto:[contact]) website: <https://ptr.just.edu.bd/>

Kruskal–Wallis tests for non-normally distributed data. Primary intervention effects across three assessment points (T1, T2, T3) will be evaluated using linear mixed-effects models (LMMs), with group specified as the between-subjects factor and time as the within-subjects factor, and pre-specified baseline covariates (age, sex, and body mass index). All covariates were measured at baseline prior to randomization and were included based on their known associations with executive function; post-randomization or time-varying covariates were not adjusted for to avoid mediation or over-adjustment bias. Although sample size estimation was based on mixed-model ANOVA, LMMs were selected for primary analysis due to their robustness to missing data and flexibility in modelling repeated measures. Model assumptions, including normality and homoscedasticity, will be assessed, and robust or rank-based alternatives will be applied if violations are detected. Significant group  $\times$  time interactions will be explored using simple main effects with Holm–Bonferroni correction for multiple comparisons. Effect sizes will be reported as partial  $\eta^2$  for mixed models and Cohen’s  $d$  (pooled SD) for pairwise comparisons, interpreted using conventional benchmarks. Within-group changes across time points will be examined using paired-samples  $t$ -tests, interpreted in relation to both statistical significance ( $p < 0.05$ ) and established minimal clinically important differences (MCID) where available. To control family-wise error across multiple primary outcomes, Holm–Bonferroni adjustment will be applied. Missing data will be handled under the assumption of missing at random (MAR) using an intention-to-treat approach with multiple imputation. Sensitivity analyses will be performed to explore the potential impact of outcome-dependent exclusions, such as participants with fewer than 50% correct responses on Go trials. Multivariate relationships among primary outcomes will be further examined using multivariate analysis of covariance (MANCOVA), adjusting for baseline covariates and assessing assumptions of multivariate normality and homogeneity of covariance matrices. This analytical strategy ensures robust, unbiased, and clinically interpretable inference in longitudinal, multigroup studies.

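### CARS-2 is required of every child with ASD at entry but is not among the model covariates; adding it is a cheap improvement, not the correction of an error

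*Protocol*

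**What the plan says.** In the Protocol, Annexure B, the eligibility row admits children aged 4–18 "with a confirmed ASD diagnosis according to DSM-5 and CARS-2, assessed by a child psychiatrist". CARS-2 is mentioned nowhere else: it is not an outcome, a covariate or a named item of the questionnaire in Annexure E.

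The statistical analysis text fixes the primary model: "Primary intervention effects across three assessment points (T1, T2, T3) will be evaluated using linear mixed-effects models (LMMs"), with group and time as factors and "pre-specified baseline covariates (age, sex, and body mass index"). It gives the reason for these three: "All covariates were measured at baseline prior to randomization and were included based on their known associations with executive function". The effect of interest is the group × time term, whose "interactions will be explored using simple main effects with Holm–Bonferroni correction for multiple comparisons".

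On missing data: "Missing data will be handled under the assumption of missing at random (MAR) using an intention-to-treat approach with multiple imputation". The variables in the imputation model are not listed.

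There is also a non-randomised comparison group: "Children in the healthy control group will undergo the same interview to confirm typical development".

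**The concern.** The covariates are justified by their link with executive function. Body mass index is on the list, while the one autism-specific measure required at entry is not. The age range is wide and no severity limit is set, so children may differ a good deal in severity.

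Two things could be at stake. The first is precision: if severity predicts the T2 score beyond what T1 already tells, leaving it out enlarges the residual variance. The second is dropout. The experimental arm is asked for five sessions a week for 12 weeks (5 × 12 = 60, as in the Annexure F tracking sheet), while the wait-list arm has biweekly discussions. With such unequal burdens, severely affected children could be lost more from one arm than the other. Missing at random holds only given the variables used in the model or the imputation, and no severity variable is named for either.

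**Working it through.** **Inputs.** The protocol supplies the entry criterion, the covariate list, the model and the missing-data approach. It gives no sample size, effect size, SD, correlation or dropout rate, so there is no figure of the plan to reproduce. Everything numerical below is an assumption. T1 is taken as the baseline measurement. ρ is the T1–T2 correlation; s is the correlation of severity with the outcome, in absolute value and the same at each time. Age, sex and body mass index are left out of the calculations.

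**Step 1: precision in a T2 model conditional on T1.** The partial correlation of severity with T2 given T1 is r = (s − ρs) / √((1 − ρ²)(1 − s²)), and adding severity multiplies the residual variance by 1 − r².

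| ρ | s = 0.3 | s = 0.4 | s = 0.5 |
|---|---|---|---|
| 0.5 | 0.967 | 0.937 | 0.889 |
| 0.6 | 0.975 | 0.952 | 0.917 |
| 0.7 | 0.983 | 0.966 | 0.941 |
| 0.8 | 0.989 | 0.979 | 0.963 |

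Worked corner: ρ = s = 0.5 gives r = 0.25/0.75 = 0.333 and 1 − 0.111 = 0.889. The cut is thus about 1% to 11%, equivalent to 1/0.989 − 1 = 1% to 1/0.889 − 1 = 12% more children. Without T1 in the model it would be s², or 9% to 25%; T1 already carries much of what severity would add.

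**Step 2: the form matters in the mixed model.** One simulated complete data set was used (80 children, three times, correlation 0.7 between times, s = 0.4, random intercept). The standard error of the group × time term at T2 was:

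- no severity: 0.19565
- severity as a main effect: 0.19565, with the estimate unchanged at −0.06045
- severity and severity × time: 0.19589

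A main effect alone does not sharpen the group × time test. Severity × time brought no gain here either, because the simulated severity effect was the same at every time; it can help only if severity predicts change. The 1–11% belongs to the model conditional on T1.

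**Step 3: bias from dropout.** A simulation of 1,000,000 children with a true effect of 0 was analysed by a T2 model with T1, then with T1 and severity. Where dropout depended on severity, the log-odds slope was 0.7 per SD, an odds ratio of e^0.7 = 2.0. The dropout patterns were:

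- Equal: 20% at mean severity in both arms, same slope (about 22% lost overall).
- One arm: 10% random loss in one arm; 25% at mean severity, with the slope, in the other (about 19% overall).
- Opposite: 20% at mean severity in both arms, slopes of opposite sign (about 22% overall).

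Absolute bias in SD units with T1 but not severity in the model:

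| ρ, s | Equal | One arm | Opposite |
|---|---|---|---|
| 0.6, 0.4 | 0.001 | 0.027 | 0.048 |
| 0.7, 0.4 | 0.000 | 0.018 | 0.032 |
| 0.7, 0.5 | 0.001 | 0.025 | 0.046 |
| 0.5, 0.5 | 0.001 | 0.042 | 0.073 |

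With severity added, every entry is at most 0.003. If severity worsens outcome and severe children leave mainly the experimental arm, the error favours the intervention.

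**Scale.** Assuming 30 children per arm (not a protocol figure) and ρ = 0.6, the standard error of the T2 contrast is √(1 − 0.36) × √(2/30) = 0.8 × 0.258 = 0.207 SD. The biases at ρ = 0.6 are then 0.027/0.207 = 0.13 and 0.048/0.207 = 0.23 of a standard error.

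**The case against.** The strongest reply is that this is a preference. The protocol pre-specifies three baseline covariates and says why they are there; it does not claim to list every correlate of executive function. A reader might infer that including body mass index and leaving out severity breaks the protocol's own selection rule. It does not: nothing in the document says severity is the stronger predictor. This objection stands, and for that reason the point is not called an error.

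A reader might also infer that severity-related dropout will bias the result, or that missing at random fails. The document does not support that. It gives no dropout figure, and equal severity-related loss produced no bias. The imputation model is unspecified and may include CARS-2 or baseline SRS-2 and ATEC; that detail usually sits in the SAP, which is not shown.

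The simulated analysis is also simpler than the planned one. A mixed model that recovers missing T2 values from T1 relies on the same assumption, so the concern carries over in kind, but its size in the three-time-point model with age, sex and body mass index has not been calculated. A plain change-score comparison of completers showed almost no bias (at most 0.004 SD) under the same assumptions, so the size depends on how T1 is used.

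Finally, the protocol does not say that a CARS-2 total is kept, or that it is newly obtained at screening. That it precedes randomisation is inferred from its role as an entry criterion. The change is therefore cheap rather than strictly free. None of these objections makes the adjustment wrong or costly.

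**Conclusion.** The point holds as a cheap improvement. The plan requires CARS-2 for every child with ASD and closes its covariate list without it. Under the assumed correlations, the gain is about 1–11% of residual variance in a T2 model that already uses T1. The possible bias is about 0.02–0.07 SD, small beside the sampling error of a trial of the assumed size. It needs two conditions together: severity-related dropout that differs between the two ASD arms, and an effect of severity on outcome beyond T1. The protocol neither establishes nor rules out either condition, though the unequal burden of the arms makes the first conceivable.

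**What to change.** - Record the CARS-2 total score at entry, not only that the diagnosis was confirmed, and do so before randomisation.
- Add it to the pre-specified covariates for the comparison of the two randomised ASD arms only. In healthy controls the score would be missing or nearly determined by group, so it should not enter a model that includes them.
- Use it either as a covariate in a T2 model conditional on T1, or as CARS-2 and CARS-2 × time in the mixed model. A main effect alone would leave the group × time test no sharper.
- Include it in the multiple-imputation model.

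The cost is one degree of freedom in the T2 model, or about three parameters in the mixed model (one main effect and two interactions for three time points), plus recording a score from an assessment that entry already requires. If the healthy controls are meant to be in the primary model, the two ASD arms also need a model of their own. The change should be made before enrolment and unblinding: a score not recorded at entry cannot be recovered later as a true baseline, and adding the covariate after unblinding would be post hoc.

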### Section II

#### ***Primary Outcome Measures***

Go/No-Go (GNG) Task

Trail Making Test (TMT)

Corsi Block Tapping Task (CBTT)

Forward Digit Span (FDS) Test

Backward Digit Span (BDS) Test

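### Within-group paired t-tests, read against p < 0.05 and the only use of the MCID, cannot separate the programme from practice or maturation and are not labelled descriptive

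*Protocol*

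**What the plan says.** All of this is in the Protocol, Annexure B (Research Methodology), mainly in the Statistical analysis entry.

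- Primary analysis: intervention effects over T1, T2 and T3 "will be evaluated using linear mixed-effects models (LMMs), with group specified as the between-subjects factor" and time as the within-subjects factor, adjusted for baseline age, sex and BMI.
- Follow-up of that analysis: significant group × time "interactions will be explored using simple main effects with Holm–Bonferroni correction for multiple comparisons".
- Then a further set of tests: "Within-group changes across time points will be examined using paired-samples" t-tests, "interpreted in relation to both statistical significance" (p < 0.05) "and established minimal clinically important differences (MCID) where available". This is the only mention of the MCID.
- The next sentence reads: "To control family-wise error across multiple primary outcomes, Holm–Bonferroni adjustment will be applied". It neither includes nor excludes the paired tests.

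Other entries of the same annexure supply the context: participants aged 4–18, a 24-week study, five instruments for executive function, and a wait-list arm that receives the programme during the 12-week follow-up. The healthy controls complete the same measures. Practice effects and maturation are not mentioned.

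**The concern.** A paired test within one group asks whether scores changed, not why. Here the same tasks are repeated in growing children, so a rise is plausible without any programme. If such a rise is significant and also passes an MCID, it is easy to report as a clinically important benefit, even when the randomised comparison shows nothing.

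Two features of the text add to this. The paired tests do not depend on a significant interaction, so they would be reported even after a null primary result. And because the MCID is tied only to within-group change, clinical importance is never judged on the difference between randomised arms. After T2 the wait-list arm is treated, so within-group change over the follow-up is especially hard to attribute.

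**Working it through.** The protocol gives no sample size, SD, correlation or expected drift, so there is no stated figure to reproduce. Everything below is conditional on assumed values, shown as a range.

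**Inputs from the protocol:** threshold p < 0.05 (two-sided assumed); three time points; three groups; five primary instruments.

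**Assumed:** n = 20, 30 or 60 per group; standardised drift dz = mean change / SD of change, from 0.1 to 0.5; no treatment effect.

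**1. Chance that a paired t-test is significant from drift alone.** The statistic follows a non-central t with n − 1 degrees of freedom and non-centrality dz × √n. For example, with dz = 0.3 and n = 30 the non-centrality is 0.3 × √30 = 1.643, the critical value is 2.045, and the rejection probability is 0.355.

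| dz | n = 20 | n = 30 | n = 60 |
|---|---|---|---|
| 0.1 | 7% | 8% | 12% |
| 0.2 | 14% | 19% | 33% |
| 0.3 | 25% | 36% | 63% |
| 0.4 | 40% | 56% | 86% |
| 0.5 | 57% | 75% | 97% |

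To relate dz to raw SD units: dz = drift / √(2(1 − r)), where drift is in SDs of the score and r is the correlation between visits. A drift of 0.3 SD with r = 0.7 gives 0.3 / √0.6 = 0.387, and rates of 38%, 54% and 84% at n = 20, 30 and 60.

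**2. Does Holm adjustment solve it?** The strictest Holm step for five outcomes is 0.05 / 5 = 0.01. At that level the rates are 9%, 15% and 38% for dz = 0.3, and 30%, 50% and 88% for dz = 0.5 (n = 20, 30, 60). They are lower, but still far above 1%, because drift is a real change and not a chance finding.

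**3. Does the randomised contrast solve it?** Change scores were simulated with equal drift in both arms (dz 0.3 or 0.5; n = 20, 30, 40 or 60 per arm; 20,000 runs each). The between-arm test of change was significant in 4.8% to 5.3% of runs. The paired test in one arm, on the same data, was significant in about 25% to 97%. Drift common to both arms cancels.

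**4. Reading one arm's p-value against the other's.** With equal drift, the chance that the experimental arm is significant and the control arm is not is p(1 − p), where p is the rejection probability. At dz = 0.3 and n = 20 this is 0.247 × 0.753 = 19%; at n = 30, 40 and 60 it is 23%, 25% and 23%.

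**5. Number of tests.** If all time pairs are tested, there are 5 × 3 × 3 = 45 tests. With no drift, no adjustment and independence, the chance of at least one p < 0.05 is 1 − 0.95^45 = 90%. If Holm is applied across the five outcomes within each group and time pair, nine families remain and the figure is 1 − 0.95^9 = 37%. Both figures are illustrative: T1–T3 change is the sum of the other two changes, so the tests cannot be independent.

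**The case against.** The strongest reply is that the protocol already has the right efficacy analysis. Intervention effects are assigned to the mixed model, and the paired tests are said only to examine within-group change. When scores truly rise, a significant paired test is a correct answer to its own question; only a causal reading would be wrong. This stands, and it limits the point to a supplementary analysis.

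Several stronger readings are tempting, and the document does not support them.

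- *That the paired tests are unadjusted.* The very next sentence applies Holm–Bonferroni across the primary outcomes. Its reach over the paired tests is unclear, and an SAP may define the family.
- *That they use only complete pairs.* The protocol plans multiple imputation as a general rule, and paired tests can be run on imputed data.
- *That the protocol treats them as proof of efficacy, or plans to compare significance between arms.* It says neither. Step 4 shows what would go wrong if a reader did so.
- *That nobody is untreated at T3.* The protocol assigns no exercise programme to the healthy controls, who complete the same measures. What is missing is an untreated ASD arm.
- *That drift alone would often produce significance.* At dz of 0.1 to 0.2 the rate is 7% to 33%. The protocol gives nothing from which to choose a value.
- *That a 90% false-positive chance applies.* It needs no adjustment and an independence that cannot hold. The 45 tests also include 15 in healthy controls, which nobody would take as programme benefit.

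What the reply does not answer is that the protocol fixes p < 0.05 and the MCID as the reading of uncontrolled change, without a descriptive label, and uses the MCID for nothing else.

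**Conclusion.** The point holds in a limited form. The within-group tests cannot separate the programme from practice or maturation, their place in the multiplicity scheme is unclear, and the MCID is attached to the wrong quantity. With no treatment effect, the chance of a significant paired test runs from about 7% (dz 0.1, n = 20) to 97% (dz 0.5, n = 60). The width of that range reflects assumed drift and sample size, not anything the protocol reports. The primary mixed-model inference is not affected. The risk lies in how secondary results would be reported, above all for lasting benefit between T2 and T3. The change should be made, but this does not undermine the trial's main analysis.

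**What to change.** Replace the paired t-tests with within-arm change estimates and 95% confidence intervals from the mixed model, labelled descriptive. Apply the MCID to the T1–T2 difference between the two randomised ASD arms, or compare between those arms the proportions of children reaching it. State that effectiveness is concluded only from that randomised contrast. If any within-group p-values are kept, say whether the Holm–Bonferroni family includes them.

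This takes a few sentences in the analysis text and needs no new data. The downside is the loss of the within-group p-values. It does not supply an untreated ASD comparison after T2, which is a feature of the wait-list design.

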| Outcome measurement   | 
Primary outcomes
 
The primary outcome will be Executive Function, assessed through three subcomponents: Inhibitory Control, Cognitive Flexibility and Working Memory. Inhibitory Control (IC) will be measured using the Go/No-Go (GNG) task; Cognitive Flexibility will be assessed with the Trail Making Test (TMT); Working Memory (WM) will be evaluated using the Corsi Block Tapping Task (CBTT), Forward Digit Span (FDS) test, and Backward Digit Span (BDS) test.
 
Secondary outcomes
 
The secondary outcomes will be social responsiveness and autism-related behavioral changes. Social responsiveness will be assessed using the Social Responsiveness Scale, Second Edition (SRS-2), and ASD-related characteristics will be evaluated using the Autism Treatment Evaluation Checklist (ATEC)
               |
| Statistical analysis  | Statistical analysis will be conducted using SPSS version 26. Continuous variables will be summarized as mean $\pm$ standard deviation (SD), and categorical variables as frequencies and percentages. Baseline differences across the three groups (two ASD intervention groups and healthy controls) will be examined using one-way ANOVA for normally distributed variables and                                                                                                                                                                                                                                                                                                                                                                                                                                                                              |

IRB of the Department of Physiotherapy and Rehabilitation established on March 27, 2024 and was approved by the departmental academic committee meeting resolution.

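### The MANCOVA does not examine the relationships it is meant to examine and, if run on all three groups, can be significant from the healthy-versus-ASD gap alone

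*Protocol*

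**What the plan says.** All references are to the protocol, Annexure B (Research Methodology).

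- **MANCOVA** (Statistical analysis): "Multivariate relationships among primary outcomes will be further examined using multivariate analysis of covariance (MANCOVA), adjusting for baseline covariates". The rest of the sentence asks for checks of multivariate normality and of equal covariance matrices. It gives no group factor, time point or contrast.
- **Covariates** (same row): the list given for the mixed model is "pre-specified baseline covariates (age, sex, and body mass index"). The T1 outcome scores are not in it, and no other list of baseline covariates appears.
- **Groups** (same row): three are named once, for the baseline comparison: "Baseline differences across the three groups (two ASD intervention groups and healthy controls) will be examined using one-way ANOVA". The mixed model is described "with group specified as the between-subjects factor and time as the within-subjects factor", without listing the levels of group. The row closes by claiming "clinically interpretable inference in longitudinal, multigroup studies".
- **Healthy children** (Eligibility criteria): they "will complete the same outcome measures to compare whether the ASD group can achieve normal developmental levels after the intervention". They are a reference group and are not randomised.
- **Where the intervention effect is tested** (Statistical analysis): "Primary intervention effects across three assessment points (T1, T2, T3) will be evaluated using linear mixed-effects models (LMMs").
- **Control arm after T2** (Intervention details): the wait-list group receives the experimental programme before the follow-up assessment.

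**The concern.** There are two separate problems.

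First, the stated purpose is to study how the primary outcomes relate to one another. MANCOVA answers a different question: whether the vector of adjusted means is the same in every group. This mismatch is in the protocol's own text and does not depend on which groups are analysed.

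Second, the sentence does not fix what is being compared. The equal-covariance check presupposes groups, and the only groups the statistical section lists are the three above. The eligibility text asks whether children with ASD can reach normal levels after treatment, so the protocol itself expects them to start below healthy children. Age, sex and BMI are not the T1 scores and cannot be expected to remove that gap. An omnibus test on three groups would then mix a non-randomised difference with the randomised one. A significant multivariate group effect on the primary outcomes could be taken as support for the intervention when the healthy-versus-ASD gap alone had produced it.

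**Working it through.** The protocol states no sample size, SD, effect or gap for these outcomes, so there is no figure of its own to reproduce. The check asks how often the omnibus test would reject if the intervention did nothing.

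**Inputs from the protocol.** Five primary tests (Go/No-Go, Trail Making, Corsi blocks, forward and backward digit span); three groups; covariates age, sex and BMI.

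**Assumed inputs.** Equal groups of 20 or 30; healthy children better by *d* SD on every test; a common correlation ρ of 0.4 or 0.5 among tests; α = 0.05; where T1 scores are used, a T1–T2 correlation of 0.6.

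**Step 1: what drives the omnibus test.** With equal correlations, the squared multivariate distance between healthy and ASD children is

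D² = d² × 5 / (1 + 4ρ).

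With *n* healthy children, 2*n* children with ASD and no intervention effect, the non-centrality of the three-group test (5 × 2 = 10 degrees of freedom) is

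λ = [n × 2n / (3n)] × D² = (2n/3) × D².

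For n = 30, d = 0.8, ρ = 0.5: D² = 0.64 × 5/3 = 1.067 and λ = 20 × 1.067 = 21.3. With ρ = 0.4: D² = 0.64 × 5/2.6 = 1.231 and λ = 24.6. Without a gap λ would be 0, so all of this comes from the non-randomised difference.

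**Step 2: simulated rejection rates with no intervention effect.** Wilks' lambda with Rao's F, covariates age, sex and BMI, 2,000 trials per cell. Where two values appear, the first is for ρ = 0.5 and the second for ρ = 0.4; single values are for ρ = 0.4.

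| Gap (SD) | Three groups, n = 20 | Three groups, n = 30 |
|---|---|---|
| 0 | 0.05 | 0.04 |
| 0.3 | 0.13 | 0.15 |
| 0.5 | 0.30 | 0.45 |
| 0.8 | 0.64 / 0.70 | 0.86 / 0.91 |

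Restricted to the two randomised arms, the test rejects in about 5% of trials whatever the gap (0.036 to 0.063 over all settings run, with or without T1 scores, including n = 40 and gaps up to 1.2 SD).

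**Step 3: does a real effect raise the omnibus rejection rate?** Not necessarily. Take n = 30, d = 0.8, ρ = 0.4. With no effect the group means are 0, 0 and 0.8, with squared deviations about their mean summing to 0.427. With a 0.5 SD effect they are 0, 0.5 and 0.8, with sum 0.327. Multiplying each by n × 5/2.6 gives λ = 24.6 and 18.9. The simulated rejection rates are 0.91 without the effect and 0.80 with it. A working intervention moves the treated arm towards the healthy children and so makes the omnibus test less likely to reject here.

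**Step 4: what cures it** (n = 30, d = 0.8, ρ = 0.4).

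- Adding the five T1 scores but keeping the three-group omnibus test: it still rejects in 0.21 of trials with no effect.
- Experimental-versus-control contrast inside the three-group model: 0.05 with no effect; power 0.44 for a 0.5 SD effect.
- Two randomised arms only: 0.05 with no effect; power 0.43 without T1 scores and 0.60 with them.

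**The case against.** The strongest reply is that the three-group reading is an inference. The protocol lists three groups only for the baseline comparison, and it describes the covariates as measured before randomisation, which fits only randomised children. The closing reference to multigroup studies and the covariance check point the other way, so the text is ambiguous. That stands: the numerical part of this point is conditional on a three-group analysis. The mismatch between purpose and method is not conditional.

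A second reply is that the MANCOVA is supplementary, the intervention effect is assigned to the mixed model, and details may be in an analysis plan that is not at hand. This limits the weight of the point. It does not excuse a stated purpose that the method cannot serve.

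Four stronger readings are tempting, and the documents do not support them:

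- *The MANCOVA will be significant.* This depends on group size and gap, neither of which is given. At a gap of 0.3 SD the rate is only about 13–15%.
- *It says nothing about the intervention.* The group factor contains the randomised contrast, and testing that contrast inside the three-group model is valid. The defect is that no contrast is specified.
- *Leaving out T1 scores biases the comparison of the arms.* Randomisation protects that comparison; the loss is precision.
- *Children missing any one test drop out.* The plan already provides for multiple imputation and exempts no analysis.

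**Conclusion.** The point holds in a limited form. MANCOVA does not examine relationships among outcomes, and the sentence leaves groups, time point and contrast open. If the three listed groups are used with age, sex and BMI as the only covariates, a significant omnibus result can reflect the healthy-versus-ASD gap alone and cannot be attributed to the intervention. With no intervention effect, false support would arise in roughly 13% to 70% of trials at 20 per group, and 15% to 91% at 30 per group, for gaps from 0.3 to 0.8 SD. These figures rest on assumed group sizes, gaps and correlations; only the direction is independent of them. The primary conclusion is not at risk from this analysis, so the change is desirable and not essential.

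**What to change.** Replace the MANCOVA sentence with one that says the following:

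1. The MANCOVA compares the two randomised ASD arms at T2 on the five primary tests. T3 is unsuitable because by then the control arm has received the programme. Alternatively, keep three groups and pre-specify the experimental-versus-control contrast as the only test bearing on the intervention.
2. The covariates are age, sex, BMI and the five T1 scores. The T1 scores are there for precision; they do not replace step 1.
3. The analysis is supportive to the mixed model.
4. Any comparison with healthy children is reported separately and as descriptive.

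If relationships among the outcomes are the real interest, report the residual correlation matrix of the five T2 scores in place of the MANCOVA.

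The cost is a few sentences and a small change to the code. The five T1 scores use five more covariate degrees of freedom per outcome. Under the assumptions above (30 per arm, 0.5 SD effect, T1–T2 correlation 0.6) that is more than repaid: power rises from 0.43 to 0.60. No extra data are needed, since T1 is already an assessment point.
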